## Aim 3: Determine the budget impact of the ACP-GV National Program

### Design

To accomplish aim 3, we will follow the steps for conducting a budget impact analysis (BIA) [24] developed by the International Society for Pharmacoeconomics and Outcomes Research (ISPOR) [25] and referenced by Smith and Barnett in their discussion of the role of economics in the QUERI program [26]. Implementation- and program-level costs will be collected and analyzed to account for the full impact of the ACP-GV program at individual sites and nationally for VHA.

### Data sources for aim 3

Data will be collected for the pre-implementation and implementation periods to estimate costs associated with ACP. VHA Managerial Cost Accounting (MCA) System data will be used to estimate health care encounter and VHA payroll costs. MCA is a derived database built from standard VHA data sources that allows comparison of cost and utilization characteristics. Activities associated with implementation (implementation period only) and direct provision of the ACP-GV will be collected at the local level and aggregated for the national program. Productivity and time data will be collected using a combination of the VA Corporate Data Warehouse, the Time Tracking Tool, and stakeholder interviews conducted as part of aim 4. Costs will be assigned to these activities based on VHA payroll costs in MCA.

### Data analysis for aim 3

ACP-GV is not expected to have direct short-term impact on overall patient healthcare utilization; therefore, the focus of the analysis will be costs related to implementation and provision of ACP-GV for sites and the National Program. Changes in costs are likely to vary by site depending on the extent to which existing resources are leveraged for provision of ACP-GV. The ability to provide ACP discussions to multiple veterans in a single session via ACP-GV will offset these increased costs; however, the extent to which these two factors exist will vary by site. To estimate direct costs, the time associated with all implementation and program activities will be multiplied by the salary and fringe rate of the team member performing the activity. Each activity will be assigned to a specific time, site, and team member to allow for estimation of costs at the individual site level. Indirect implementation costs (e.g., educational materials) will be tracked and allocated to sites by the ACP-GV Implementation Team.

To examine the budget impact at existing sites, we will compare the costs associated with ACP during the year before and after the site joined the ACP-GV National Program. Cost differences will be analyzed from the payer perspective [24]. For the national program, including all ACP-GV program costs and costs attributed to the implementation strategies identified in Table 1, VHA will be the payer. For program and implementation costs specific to a VAMC, the VA Medical Center (VAMC) budget administrator will be considered the payer. Observable characteristics that are predicted to influence the ACP budget of an individual site will be collected (e.g., VAMC size). Using TreeAge software, a probabilistic sensitivity analysis (PSA) will be conducted [27]. The PSA allows the assignment of a distribution to model parameters rather than just a point estimate to account for uncertainty in the BIA model. To facilitate broader implementation of ACP-GV, a decision analysis model is needed for non-participating sites to estimate the budget impact at their site based on site-specific factors (e.g., VAMC size). The model will be developed in Microsoft Excel, and a user guide will be created and disseminated to sites. This model will show the budget impact at existing ACP-GV sites as well. One-way sensitivity analyses will be possible within the model to allow decision-makers to see the impact of each site-specific factor.

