## Aim 1: Evaluate the impact of the ACP-GV National Program on the proportion of ACP discussions in VHA by comparing ACP-GV sites to propensity score-matched control sites not implementing ACP-GV

### Design

The 35 ACP-GV sites will be considered “intervention” sites. We will identify a set of matched “control” sites (*N* = 35) defined as VHA facilities not implementing ACP-GV based on an analysis of the ACP-GV workload specific code in VA Corporate Data Warehouse data and not participating in the National Program implementation activities but documenting ACP discussions as noted in the VA Corporate Data Warehouse and using AD note titles. Our hypothesis is that ACP-GV sites (i.e., intervention sites) will have a higher proportion and significantly greater quarterly and annual rates of ACP discussions compared to the PS-matched control sites. Given that the sites were not randomized to either the intervention or control, we will use PS matching to create a “pseudo” randomized evaluation design. The PS is a model-based conditional probability of a site’s membership in the intervention, given its observed site characteristics [21]. We will use a logit model to estimate the PS for each site. The dependent variable of the logistic regression model is being/not being in the ACP-GV intervention group. The independent variables are site characteristics including: rurality, geographic location, Veterans Integrated Service Network (VISN), staffing, facility size, and aggregate veteran demographics such as age, gender, and race/ethnicity. We will use a greedy matching algorithm based on 5-to-1 digit matching [22]. An initial ACP-GV site will be randomly selected from the existing sites to start the process. A non-ACP-GV site (i.e., control) with the closest PS that lies within a fixed distance will be selected for matching. If multiple control sites have PS that are equally close, then one of the control sites will be selected at random. The process will continue until all ACP-GV sites that can be matched have been matched. To evaluate the success of the PS matching, we will compare the balance in the distributions of all the observed site covariates between the two groups using standardized difference plots. An absolute standardized difference of less than 10% suggests a negligible imbalance between the two groups for a given site covariate [23]. A PS matching limitation is if no control sites have PS that lie within the predefined distance (i.e., caliper) of an intervention site, then that ACP-GV site is not included in the PS-matched sample. Given sample size limits, if the PS matching produces a limited number of pair matches, we will consider other strategies, (e.g., PS through stratification, covariate adjustment with PS, or inverse PS weighting).

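### Aim 3 takes the offset in existing ACP costs from an uncontrolled before/after comparison, so background change in ACP activity or pay is counted as part of the offset

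*Protocol article*

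**What the plan says.** The Design section of aim 3 in the protocol article sets the scope: costs are gathered "to account for the full impact of the ACP-GV program at individual sites and nationally for VHA". Under *Data analysis for aim 3*, the contrast is introduced with "To examine the budget impact at existing sites" and reads "we will compare the costs associated with ACP during the year before and after the site joined the ACP-GV National Program". Differences are taken from the payer's perspective. Uncertainty is handled by a probabilistic sensitivity analysis on model parameters, and the planned spreadsheet model allows one-way analyses on site-specific factors.

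The same section expects savings that work against the added costs: "The ability to provide ACP discussions to multiple veterans in a single session via ACP-GV will offset these increased costs". It adds that the balance will differ between sites.

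On data, *Data sources for aim 3* says that "VHA Managerial Cost Accounting (MCA) System data will be used to estimate health care encounter and VHA payroll costs", and that "MCA is a derived database built from standard VHA data sources that allows comparison of cost and utilization characteristics". Implementation activities are recorded for the implementation period only. Direct costs are recorded time multiplied by the pay and fringe rate of the person doing the work.

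The Design section of aim 1 plans comparison facilities: "We will identify a set of matched “control” sites (*N* = 35) defined as VHA facilities not implementing ACP-GV". These sites do not take part in the National Program, "but documenting ACP discussions as noted in the VA Corporate Data Warehouse and using AD note titles". Aim 3 does not use them.

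**The concern.** A before/after difference equals a programme effect only if costs would otherwise have stayed flat. Every site has ACP costs before it joins, because the background section on why ACP is done in healthcare settings describes ACP discussions as mandated in all VHA settings. Those costs can move for reasons unrelated to the group visits, such as pay changes or a system-wide shift in ACP activity or its recording. The same section mentions a new national data system for advance directives launched in FY 20. Sites are also at varying stages of implementation, so their two-year windows may cover different calendar periods, and differences between sites may partly reflect calendar time.

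At stake is the offset, which decides whether group delivery recovers part of its own cost. It is the component that a trend can distort, and a small net impact is distorted most in relative terms.

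**Working it through.** The document states no cost or budget-impact figure for aim 3, so there is nothing to reproduce. The check is algebraic, followed by an illustration on assumed values.

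**Components of the before/after difference at one site**

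- I: directly costed implementation and group-visit delivery. It has no counterpart before joining, so it carries no trend in individual ACP volume.
- P: the true programme-caused change in other ACP provision cost (negative if group visits save money). This is the offset.
- C0: ACP cost in the year before joining.
- s: relative change in that cost that would have happened without the programme.

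Planned estimate = I + P + s × C0.

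True impact = I + P.

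Bias = s × C0, all of it in the offset, which is read as P + s × C0.

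Relative error in the net impact = s × C0 / (I + P). It grows as savings bring I + P towards zero.

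**Illustration (every input assumed; index units):** C0 = 100, I = 20. Cells show the planned estimate and its relative error.

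| P | True I + P | s = -5% | s = 0 | s = +2% | s = +5% | s = +10% |
|---|---|---|---|---|---|---|
| 0 | 20 | 15 (-25%) | 20 (0%) | 22 (+10%) | 25 (+25%) | 30 (+50%) |
| -10 | 10 | 5 (-50%) | 10 (0%) | 12 (+20%) | 15 (+50%) | 20 (+100%) |
| +10 | 30 | 25 (-17%) | 30 (0%) | 32 (+7%) | 35 (+17%) | 40 (+33%) |

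Example, second row, s = +10%: 20 - 10 + 0.10 × 100 = 20, against a true 10. The offset itself would be read as -10 + 10 = 0, so the saving disappears. At s = -5% it would be read as -10 - 5 = -15.

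If comparison sites share s, subtracting s × C0 returns I + P in every cell.

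**Do the planned safeguards remove the bias?** No. The probabilistic analysis varies model parameters, and the one-way analyses vary site factors such as facility size. Neither separates a common time trend from the programme.

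**Which costs are in the contrast?** One sentence under *Data analysis for aim 3* narrows the focus to implementing and providing the group visits. The before/after sentence covers the wider set of ACP-associated costs. The wider set is the one exposed to trend, and it is needed to see an offset at all.

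**The case against.** The strongest reply is that aim 3 is a budget analysis and not an effect estimate. A payer does spend the realised pay increases, so the before/after difference is a legitimate cash figure. That stands, and the figure should be kept. It does not answer the question about the offset, which the protocol attributes to group delivery.

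A reader might infer that aim 3 credits the entire change in ACP cost to the programme. The document does not support this: implementation and delivery costs are built up activity by activity and are not exposed to a trend in individual ACP volume.

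A reader might also infer that the error is passed on to non-participating sites through the spreadsheet model. The article says that model works from site-specific factors. It does not say that the model is calibrated on the before/after differences, so this route is only possible. Nor can a dollar amount, per site or nationally, be attached to the bias.

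The article's silence on a price year is not a defect in itself, since an article commonly leaves that to the full protocol.

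The practical objections have weight. Aim 1 drops sites without a match within the caliper and may switch to stratification, covariate adjustment or weighting, so some sites may have no matched pair. Matching uses site characteristics, not earlier cost or cost trend, so a common trend is an assumption. Time-tracking and interview data are described only for ACP-GV sites. That MCA covers the comparison facilities, and can isolate ACP cost there, is an inference from its description. These points limit the remedy to part of the costs but do not remove the reason for it.

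**Conclusion.** The point holds for the offset component only. The stated contrast has no comparator, and the offset it yields carries a bias of s × C0, zero only if ACP costs at the joining sites would have stayed flat. Size and sign are not derivable from the document, and the index figures show only how the error scales. The directly costed components and the cash view are sound for their purposes. This is a worthwhile, inexpensive addition to aim 3, not an error that invalidates it. The conclusion rests on the contrast covering all ACP-associated costs, as its wording says, and the remedy rests on comparison sites sharing the background trend.

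**What to change.** Keep the before/after figure and label it the payer's cash view. Add a control-adjusted estimate of the offset:

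- Restrict it to encounter and payroll components obtainable from MCA and the Corporate Data Warehouse. Leave time-tracked implementation and delivery costs as direct additions.
- Subtract the change at the aim 1 comparison sites over the same calendar window. Use the matched pair where one exists, otherwise the pooled or weighted aim 1 control group. Where baselines differ, apply the controls' relative change to the site's own pre-joining cost.
- Hold pay rates at one price year for this estimate.
- State which date anchors the window. *Data collection for aims 1 and 2* uses first use of the workload code and discussion note, whereas *Data analysis for aim 3* uses the date of joining.
- If the spreadsheet model draws on the before/after differences, use the adjusted estimate for its offset parameter.

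The cost is one further extract (assuming MCA covers the control facilities) and one table. The downsides are a wider interval, dependence on a common trend, and no adjustment for costs captured only by the Time Tracking Tool or interviews.

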## Aim 4: Identify the characteristics of high-performing (e.g., high rates or sustainers) and innovative sites (e.g., unique local program design or implementation of ACP) to inform sustainability and further spread

### Sampling plan

We will purposively select approximately 24 ACP sites. We will use site reports and our aims 1 and 2 VA Corporate Data Warehouse datasets to identify a total of six sites with high-performing characteristics (i.e., three sites with high productivity in terms of ACP-GV against the performance goal of 200 ACP-GV groups a year/per FTEE and three sites with high rates of AD discussions in the 75th or higher percentile nationally) and six sites that are sustainers after the intensity of implementation strategies begins to reduce (i.e., three sites that meet the ACP-GV performance goal and three sites with high rates of AD discussions). To capture unique site-specific program design or other innovations that might be missed by identifying sites based only on performance, we will identify six sites based on unique local program design characteristics and six with innovative models for implementing ACP known to the ACP-GV Leadership or Implementation Team or from data in the ACP-GV Implementation Team Site Tracking Report.

### Data collection for aim 4

Currently, the ACP-GV National Program and Implementation Team host weekly educational calls for all sites. The Implementation Team routinely tracks training participation at the individual and site level and records it on the ACP-GV Implementation Team Site Tracking Report. Prior to starting aim 4 interviews, we will recruit sites on these calls by describing the opportunity for ACP-GV site personnel who are implementing the program to participate in interviews. We will conduct semi-structured qualitative interviews with the main implementer of ACP-GV at each selected site. These primary points of contact are tracked on the Site Tracking Report as participating in the ACP-GV National Program’s activities. Given that our operational partners deemed this evaluation to be quality improvement and non-research, the ACP-GV Implementation Team will send an e-mail, a copy of an information sheet, and the interview guide to invite the main implementer at the ACP-GV sites to participate. After confirming willingness to participate, a trained qualitative interviewer will conduct the 45-min interview by telephone. To speed the process of transcription, a trained data entry assistant will digitally record this interview using a VHA approved recorder. Interviews will be transcribed verbatim by the data entry assistant (who will also be on the call) and checked against their notes. The interviewer will then prepare an interview report and provide it back to the interviewee for member checking. In order to attain targeted recruitment numbers, the interviewer will work closely together with the ACP-GV Implementation Team in weekly meetings to determine which sites qualify in each category and to discuss the sites’ level of participation. If participation is low, we will ask the ACP-GV National Program to encourage participation verbally on the calls and in their email correspondence with sites.

### Data sources for aim 4

The interview guide will be developed using the Consolidated Framework for Implementation Research (CFIR) Interview Guide Tool and includes the following constructs related to implementation, sustainability, and spread: (1) intervention characteristics: adaptability, cost; (2) outer setting: external policies and incentives; (3) inner setting: networks and communications, relative priority, organizational incentives and rewards; (4) readiness for implementation: leadership engagement, available resources; (5) process: planning; (6) engaging: opinion leaders, reflecting and evaluating. Additional questions to be developed with input from the ACP-GV Leadership and Implementation Teams will focus on ACP-GV specific information on implementation and sustainability, as well as unique characteristics and innovations. Additional questions about the individual and set of implementation activities used, those not used, and rationales for each will be informed by the ACP-GV monthly site reports.

### Data analyses for aim 4

The coding team will include a doctoral trained qualitative interviewer/analyst, a data analyst, and a data entry assistant. We have divided the qualitative data analysis process into four steps: (1) data management: transcripts of the audio-recordings will be entered in Atlas-ti, a software program already on hand that enables analysts to mark blocks of text with codes. Coding will use systematic, iterative, and directed content analysis methods [28, 29]. Upon completion of independent coding by at least two coders, all the transcripts from multiple coders will be merged into one hermeneutic unit. (2) Development of top-level codes: following a deductive approach guided by domains identified from CFIR [30], we will use a two-tiered coding strategy (e.g., top- and sub-level). The team will follow the conceptual framework of the CFIR model and use the interview guide to develop a preliminary code book. (3) Top-level coding: the coding team will independently assign top-level codes to one-half of the transcripts using the preliminary code book, paying attention to themes that relate to performance and sustainability. To ensure coding reliability and consistency, the lead evaluator on the project will review initial and all final coding.

We will also use the Coding Analysis Toolkit (CAT) software to run comparative statistics estimating team consensus in applying top-level codes. If the results do not meet the acceptable reliability criterion of 0.70 or higher, the team will meet to resolve differences. This process will be repeated until coding consistency at or above the acceptability level is achieved, after which the three coders will work independently. (4) Sub-level coding: the team will sub-code top-level codes that are “grounded” (i.e., associated with many quotations). Sub-level coding will follow a similar trajectory to that of top-level coding. After coding is complete, the team will select quotations that illuminate sustainability, innovation, and uniqueness and write summary statements and outline overarching themes across questions and codes, noting any repeating patterns or divergent ideas. Interpretation of the data will compare, contrast, and develop these overarching themes and prepare the summarized data into a final report highlighting variation to include unintended consequences of ACP-GV implementation and sustainability, as well as high-performing and innovative models of ACP. Lessons learned will be drafted from the strengths and limitations of the ACP-GV program. To integrate the quantitative and qualitative data, we will merge data from aims 2 and 4 to refine the existing ACP-GV implementation manual to include sustainability and spread. We will refine the manual in concert with the ACP-GV Implementation Team.

### Trial status

The Institutional Review Board at Central Arkansas Veterans Healthcare System has approved this program evaluation. Data collection for this program evaluation began in October 2019.

## Discussion

This mixed methods program evaluation will produce an impact analysis on the funding of staff positions to implement, sustain, and spread a program, Advance Care Planning (ACP) via Group Visits (ACP-GV), nationally across the entire US Department of Veterans Affairs (VA) healthcare system. To determine the impact of the National Program, we will use a propensity score-matched control design to compare ACP-GV and non-ACP-GV sites on the proportion of ACP discussions in VA healthcare facilities (aim 1). To account for variation in funding status, we will document and compare funded and unfunded sites on the effectiveness of implementation strategies (individual and combinations) used by sites in the National Program on ACP discussion and advance directive completion rates across the VHA (aim 2). In order to determine the fiscal impact of the National Program and to help inform future dissemination across VA, we will use a budget impact analysis (aim 3). Finally, we will purposively select, recruit, and interview key stakeholders, who are clinicians and clinical managers in the VHA who offer ACP discussions to veterans, to identify the characteristics of high-performing (e.g., high rates or sustainers) and innovative sites (e.g., unique local program design or implementation of ACP) to inform sustainability and further spread (aim 4).

This evaluation will rely on quantitative and qualitative methods to evaluate the impact of a set of five implementation strategies deployed by the ACP-GV National Program, primarily through using the CFIR [31]. The strategies are as follows: (1) provide new funding for new or dedicated staff positions who deliver ACP-GV in rural VHA facilities and CBOCs, (2) create a learning collaborative among sites, (3) conduct ongoing training with sites, (4) identify and prepare champions, and (5) conduct audit and feedback with sites using national VA administrative data. There are three main data sources for this QUERI partnered evaluation: (1) the VA Corporate Data Warehouse data base, which contains VHA national ACP and AD data at the patient, provider, clinic, and facility level; (2) ACP-GV Implementation Team Site Tracking Reports, which are monthly reports on ORH mandatory data elements and national data collected on the sites’ participation in the ACP-GV National Program and its implementation activities; and (3) ACP-GV Evaluation Team qualitative interviews, which will collect data on budget impact and implementation challenges, successes, unexpected outcomes, and unintended consequences from ACP-GV implementation. As an observational implementation evaluation, the next steps for this QUERI-partnered evaluation will be to examine the natural variation in implementation and spread of ACP-GV as it rolls out to all VHA facilities across the country.

In order to determine the most effective and efficient delivery mechanism that can be sustained beyond funding staff positions, it is essential to evaluate the impact of funded staff positions as a discrete implementation strategy or if the impact is contingent on the combination with other implementation strategies, on implementation effectiveness and cost outcomes. While this study focuses on the implementation of an EBP in a national health care system within the VA, this program is of enormous value to other health care systems who offer ACP as part of routine service delivery and preparation for health care decision-making with patients and families who may or may not have a surrogate decision-maker identified. Future studies on ACP in other non-VA health care systems need to consider carefully the development of administrative data to capture non-reimbursable services such as ACP and the barriers and facilitators to the use or non-use of ADs on patient, providers, ethics teams, and health care utilization, patient satisfaction, and cost outcomes. Regardless of the program used to conduct ACP, this protocol fills a gap in the evidence base regarding the impact of specifically using funded positions as an implementation strategy and represents unique challenges and opportunities to implementing EBP in health care settings. We anticipate that this program evaluation will provide our operational partners with immediate and actionable information to plan for sustainability when funding for extra staff positions in predominately rural areas is no longer an option. Going to scale with an EBP with or without funded staff positions dedicated to the program is a critical decision-making issue for clinical managers and leaders to consider in mission driven and resources constrained health care systems.

